### Interventions

Transcutaneous electrical stimulation will be applied to the acupuncture points in the intervention group, and the control group will not have TEAS. Based on the nature of chronic disease and barrier of time necessary for frequent transportation to hospital, the majority of treatment during 12 weeks will be operated by participants themselves at home. And participants may distinguish whether the instrument is on or not. It is difficult to blind the participants. Hence, we do not set sham therapy as the control group. Both groups will be educated about lifestyle modification because the guidelines clearly recommend that lifestyle changes should be basic treatments at high-normal blood pressure.

#### TEAS

A household transcutaneous nerve stimulator (SDP-330; Yuwell, Suzhou Medical Appliances Co, Ltd., Suzhou, China) with two 100-Hz output channels at a pulse width of 0–100 μs will be used for the application of TEAS. It has 10 different stimulus intensities, and the intensity of the stimulation will be individually adjusted by the participants with the recommendation to increase the intensity gradually to trigger the maximum sensory threshold without discomfort or pain. The self-adhesive electrodes measuring 5 × 5 cm will be placed on the acupuncture points region. The stimulator has 8 different modes, but the participants will be asked to select one of the “press” or “knock” or “knead” mode, which cannot be changed during treatment. The participants will be asked to keep a treatment diary and register the time of stimulation.

The following four bilaterally acupoints with relevance for BP lowering according to traditional Chinese medicine concepts determined by a literature review [25] will be used in the intervention group: *Hegu* (LI4), *Quchi* (LI11), *Zusanli* (ST36), and *Taichong* (LR3) (Table 1 and Fig. 1). Traditional Chinese medicine believes that *Yin* and *Yang* rise and fall orderly, harmonize of *Qi* and blood, and normalize blood pressure under normal physiological conditions. Worry and anger, improper diet, or fatigue and internal injury can cause the imbalance of liver and kidney, *Yin* and *Yang*, viscera dysfunction, endogenous wind and heat, and *Qi* and blood adversity and raise blood pressure. The above acupuncture points are considered to regulate viscera, balance *Yin* and *Yang*, harmonize *Qi* and blood, and regulate blood pressure to restore normal [26]. Some of the acupoints were supported by previous studies which used the TEAS treating *Hegu* and *Quchi* on the forearm and showed significant reduction in blood pressure [23, 24]. In previous study, we founded that acupuncture at *Taichong* decreases high blood pressure and nicotinamide adenine dinucleotide phosphate oxidase in the rostral ventrolateral medulla of spontaneously hypertensive rats [27], and the other study suggested that the beneficial effects of electroacupuncture at *Zusanli* on hypertension may be through modulation of functional γ-aminobutyric acid receptors in the nucleus tractus solitarii [28]. The clinical efficacy of these two acupoints has also been confirmed in a multicenter clinical trial [29]. Furthermore, these 4 points were on the limbs so it is very easy for participants to access and apply treatments.

**Table 1 Tab1:** Locations of acupoints in intervention group

Acupoints	Locations
*Hegu* (LI4)	On the dorsum of the hand, radial to the midpoint of the second metacarpal bone.
*Quchi* (LI11)	On the lateral aspect of the elbow, at the midpoint of the line connecting LU5 with the lateral epicondyle of the humerus.
*Zusanli* (ST36)	3 cun^a^ directly below *Dubi* (ST35), and one finger-breadth lateral to the anterior border of the tibia.
*Taichong* (LR3)	In the depression anterior to the junction of first and second metatarsal bones.

^a^1 cun (≈20 mm) is defined as the width of the interphalangeal joint of patient’s thumb

**Fig. 1 Fig1:**
[figure not shown]
Four bilaterally acupoints with relevance for BP lowering according to traditional Chinese medicine concepts

The first treatment will be at LI4 and LI11 on the same arm for 15 min, followed by the same acupoints on the opposite arm for 15 min. The second treatment will be at ST36 and LR3 on the same leg for 15 min, and then the same acupoints on the opposite leg will be taken for 15 min. Each treatment will last a total of 30 min, and different acupoints will be used. Participants will be asked to alternate treatment on alternate days to guarantee they will receive 4 times TEAS per week and 48 times in total and cannot increase or decrease the number of times.

Each participant in the intervention group will receive a stimulator with written instructions as well as the participants’ manual on how to do the TEAS treatment properly. Treatment will be performed at the participants’ home, and TEAS will be performed by the participants. At the beginning of the trial, the study investigators will instruct the participants to locate the acupoints. Participants will be asked to take photos to provide feedback to investigators during the initial treatment, to ensure that participants can accurately find all 4 acupoints. In addition, acupoint pictures and videos will be produced to assist participants. Study investigators will ensure the participants fully understand the operation of TEAS and the location of acupoints. Figure 2 shows the study design.

**Fig. 2 Fig2:**
[figure not shown]
Study design

#### Lifestyle modification

Participants in both groups will receive recommendation for lifestyle modification. All participants will receive relevant weekly information through the WeChat app (Tencent, Shenzhen, China) in mobile phone and monthly educational activities in the community. They contain information about weight control, increase physical activity, healthy eating, dietary sodium reduction, smoke abatement, and set limit to alcohol. This approach was supported by previous study which used a WeChat-based lifestyle modification in China and showed significant reduction in blood pressure for patients with hypertension [30].

### Outcomes

#### Primary outcome

The primary outcome will be the change in mean SBP from baseline to 12 weeks.

BP will be measured as proposed by the 2018 Chinese Guidelines for Prevention and Treatment of Hypertension [10]. Participants will be asked to avoid exercise, alcohol, cigarettes, and coffee/tea for at least 30 min before the BP measurement. BP will be measured with the participant in a seated position after 5 min of quiet rest. Participants will be required to take blood pressure measurement. A digital BP monitor (HEM-7136, OMRON Corporation, Kyoto, Japan) with suitable cuff size will be used. Clinicians will record three sequential BP readings at 5-min intervals, and the final BP will be calculated by removing the initial reading and calculating the mean from the two remaining readings.

#### Secondary outcomes

##### Changes in mean blood pressure at other time points

Other secondary outcomes include measures of changes in mean SDP and DBP from baseline to 4, 8, 12, 24, and 36 weeks.

##### Proportion of progression to hypertension

The proportion of subjects with hypertension (BP > 140/90 mmHg) will be calculated among the high-normal BP participants at 12, 24, and 36 weeks.

##### Quality of life (QoL)

The 12-item Short Form Health Survey (SF-12) [31] will be used for quality of life at baseline, 12, 24, and 36 weeks. The questionnaire consists of a mental domain and a physical domain (each domain ranges from 0 to 100), and a higher score will be considered to indicate a better quality of life.

##### Body mass index (BMI) and waist circumference

Net change in BMI and waist circumference will be measured at baseline, 12, 24, and 36 weeks. The BMI, defined as the weight (kg) divided by the participant’s height squared (m^2^) [32], will be calculated as an index for obesity. And the waist circumference will be measured (at the smallest circumference between the iliac crest and the lower costal margin) in centimeters (cm).

##### Adverse events (AEs)

Any AEs will be monitored and documented throughout the trial by the investigators and participants. Based on their potential association with the TEAS procedure, AEs will be categorized by specialists as treatment-related or non-treatment-related within 24 h of occurrence. Potential AEs of TEAS used in the trial include continuous post-electrostimulation sensation and skin numbness. The schedule of enrolment, intervention, and assessments is shown in Fig. 3. If acute or uncontrolled hypertension or other serious adverse reactions occur, the participants will be asked to discontinue from this trial and seek medical attention immediately.

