#### Statistical analysis

Analysis will be carried out on an intention-to-treat (ITT) basis and will be performed using SPSS 23.0 statistical software (IBM SPSS Statistics, New York, USA) with a 2-sided *P* value of less than 0.05 considered significant. The measurement of data that conforms to the normal distribution will be expressed as mean ± SD, the measurement data that does not conform to a normal distribution will be expressed by the median (interquartile range), and counting data will be represented by cases (percentages). The continuous variables will be evaluated by using a *t* test or the Mann-Whitney *U* test for comparison. The chi-square test or Fisher’s exact test will be employed to compare binary variables. Missing data will be imputed using the last observation carried forward.

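### A participant withdrawn for hypertension between visits may be scored as not progressed, because blanket last-observation-carried-forward can replace the raised BP with an earlier high-normal one

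*Protocol article*

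**What the plan says.** Four statements in the protocol article bear on this point.

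- Under Adverse events: "If acute or uncontrolled hypertension or other serious adverse reactions occur, the participants will be asked to discontinue from this trial". The discontinuation is from the trial, not only from TEAS. The trigger has no BP threshold.
- Under Proportion of progression to hypertension: "The proportion of subjects with hypertension (BP > 140/90 mmHg) will be calculated". The visits named are weeks 12, 24 and 36, so this is a proportion at each of three visits.
- Under Statistical analysis: "Missing data will be imputed using the last observation carried forward". No exception is made for any outcome or any reason for missingness. The same paragraph says: "Analysis will be carried out on an intention-to-treat (ITT) basis".
- Under Changes in mean blood pressure at other time points: "changes in mean SDP and DBP from baseline to 4, 8, 12, 24, and 36 weeks". BP is therefore scheduled every 4 weeks to week 12 and every 12 weeks after that.

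Adverse events are documented throughout, but nothing links that record to the progression outcome. Nor does the article say whether an unscheduled reading counts as an observation, or whether BP is still measured after discontinuation.

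**The concern.** The withdrawal trigger overlaps with what the progression outcome is meant to detect, so missingness here depends on the outcome. Take a participant whose last scheduled reading was high-normal and who is found between visits to have uncontrolled hypertension. The participant is asked to leave, later visits are missing, and the carried-forward value is the high-normal one. Followed as written, the rules score a non-event at each remaining time point. A withdrawal of this kind before week 12 also puts the earlier, lower SBP into the primary outcome.

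Participants and the staff who deal with them are unblinded, and the trigger is left to judgement, so such withdrawals could differ between arms. The pilot is also meant to supply figures for sizing a later trial, so misrecorded rates and SBP values would carry into that calculation.

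**Working it through.** **Plan's own figure.** Sample size: 2 × 30 = 60, which reproduces. It comes from a rule of thumb. The article gives no progression rate, effect size or dropout assumption, so there is no power calculation to reproduce.

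**Which value is carried forward.** There are two cases.

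1. The raised BP is recorded at a scheduled visit and the participant then leaves. The last observation exceeds 140/90, it is carried forward, and the event is counted.
2. The raised BP is found between visits and not entered as an outcome reading. The last observation is the previous scheduled value, or baseline. Entry requires SBP 120–140 and/or DBP 80–90 mmHg, which on the intended high-normal reading is a non-event under the above-140/90 rule.

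Only case 2 loses events. It is most plausible in the 12-week gaps after week 12.

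**Size per event.** 1/30 = 3.3 percentage points in one arm.

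**General form.** Let p be the true progression proportion, w the share of progressors withdrawn under the adverse-event rule, and u the share of those with no scheduled reading above 140/90 recorded first. Then

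counted events = 30 × p × (1 − w × u).

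The article gives none of p, w or u. With assumed true rates of 30% (control) and 15% (TEAS), the same loss in both arms, and approximate power at two-sided 0.05:

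| w | u | 1 − wu | Control events | TEAS events | Risk difference (points) | Power |
|---|---|---|---|---|---|---|
| any | 0 | 1 | 9.0 | 4.5 | 15.0 | 28.2% |
| 0.10 | 1 | 0.90 | 8.1 | 4.05 | 13.5 | 25.2% |
| 0.25 | 0.5 | 0.875 | 7.88 | 3.94 | 13.1 | 24.5% |
| 0.5 | 0.5 | 0.75 | 6.75 | 3.38 | 11.25 | 21.0% |
| 0.5 | 1 | 0.50 | 4.5 | 2.25 | 7.5 | 14.7% |

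The risk ratio (TEAS to control) stays at 0.5 in every row. All events vanish only if w = u = 1.

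**Equal against unequal loss, assumed counts.** Start from 6/30 (20.0%) control and 3/30 (10.0%) TEAS.

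- One third lost in each arm: 4/30 and 2/30. The difference falls from 10.0 to 6.7 points and the ratio is unchanged.
- Two lost in control only: 4/30 = 13.3% against 10.0%. Difference 3.3 points, ratio 0.75.
- Four lost in control only: 2/30 = 6.7% against 10.0%. The direction reverses.

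The last two lines show what unequal loss can do. The article gives no reason to expect that pattern.

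**Primary outcome.** If a participant withdrawn before week 12 has a carried-forward SBP lower than the true value by d mmHg, the arm mean falls by d/30 mmHg. No d can be taken from the article.

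**The case against.** A reader might infer that everyone who progresses is removed and erased. The article does not support that, for two reasons. First, the method carries forward whatever was last observed, so a raised reading at week 4, 8, 12, 24 or 36 survives. Second, the trigger is grouped with serious adverse reactions and is not equated with BP above 140/90. A participant slightly above that level may never meet it, may stay in the trial, and would then be counted normally. Both points stand and make the claim conditional.

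A reader might also infer that the TEAS arm would end up looking worse than control. That requires a larger proportional loss in control, which nothing in the article establishes.

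Nor does the discontinuation rule flatly contradict the ITT statement. Withdrawn participants stay in the denominator through imputation, contact details are kept for missed visits, and the article does not expressly say that BP measurement ends. The full protocol, the schedule figure and any SAP are not shown and may say more.

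Finally, proportions at fixed visits are a legitimate outcome, matching the follow-up times for quality of life, BMI and waist circumference. Replacing them with cumulative incidence over all visits would be a different outcome, and the defect does not require it.

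What remains is that the article itself fixes last-observation-carried-forward without exception and asks these participants to leave the trial. An unseen SAP could add an exception, but that would depart from the published rule, and it could not recover BP that was never measured.

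**Conclusion.** The point holds conditionally. Taken together, the adverse-event, progression and missing-data rules may record a participant withdrawn for hypertension as not progressed, and may put too low an SBP into the week-12 comparison, when the raised BP was not captured at a scheduled visit. Where it was captured, nothing is lost.

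The loss cannot be estimated from the article. It ranges from none (u = 0) to a halving of counted events at w = 0.5 and u = 1, all under assumed values. The misclassification shrinks the risk difference if proportional loss is equal, and biases both difference and ratio if it is not.

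Severity is moderate. The progression outcome is secondary, and the trial is a 60-person pilot with only about 28% power for 30% against 15% even with no loss. The primary outcome is touched only by withdrawals before week 12. The events would still appear among the adverse events, although they would not enter the efficacy comparison.

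**What to change.** Leave the clinical action as written; no view is taken on when a participant should be discontinued. Reconcile the three sections on the data side:

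1. Count withdrawal for acute or uncontrolled hypertension as progression at that and all later time points. Keep the existing above-140/90 rule for measured BP. Changing it to at or above would score an eligible participant unchanged at 140 or 90 as progressed.
2. For these participants, do not carry a pre-withdrawal high-normal SBP forward. Use the BP recorded at the withdrawal event where there is one. Where there is none, report a sensitivity analysis over a stated range of values.
3. Use any BP still collected at scheduled visits in the ITT analysis.

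The cost is outcome and missing-data wording, plus retrieval of the reason for withdrawal and the BP from the adverse-event records. The downside is that progression becomes a composite of measured BP and withdrawal for hypertension, so the two components should be reported separately as well.

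Under Trial status, all 60 participants are reported as randomized and follow-up was expected to end in November 2020. Item 3 therefore helps only where such readings exist. Items 1 and 2 can be set before the unblinded analysis; if that has already been run, they should be reported as post hoc sensitivity analyses.

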**Fig. 3 Fig3:**
[figure not shown]
Schedule of enrolment, intervention and assessments

##### Quality assurance and quality control

To guarantee the quality of the study, the trial protocol was reviewed and revised by experts in hypertension, acupuncture, methodology, and statistics. A pre-specified standard operating procedure of BP measurement, including selection of appropriate cuffs, reading and calculation of mean BP, and maintaining and calibrating of electronic sphygmomanometer, will be developed to reduce measurement error. Other standardized procedures for the operational aspects of the study including details in filling out questionnaires, recruitment, lifestyle intervention coaching, assessment of AEs, and data management will also be used to train the study personnel. The clinical research associate (CRA) will review the data regularly, for authenticity and timeliness of data collection and data quality. All data will be collected onto paper questionnaires and then transferred to an Excel spreadsheet and will be preserved for at least 5 years after publication of the trial results. Hence, all data collected during the course of the research will be kept strictly confidential and only accessed by the study staff. The private information of patients including the name and telephone number will be critically protected and will never be allowed to be disclosed. If reviewers or readers have any questions regarding our published data, or if any researcher will conduct meta-analyses, they can contact the corresponding author for access to the anonymized data. Detailed instructions, acupoint pictures, videos, and treatment procedures of the TEAS will be produced and distributed to each participant in the intervention group. Study investigators will ensure participants’ compliance with the intervention protocol. Participants will be registered with a phone number and address for further contact in case of missing outlined visits.

### Statistical methods

#### Sample size

This pilot study aims to assess the effectiveness and safety of TEAS combined with lifestyle modification for high-normal BP and determine the feasibility of a further large clinical trial. The minimum sample size for exploratory trials is 20 to 30 per group according to Provisions for Drug Registration in China. It is generally accepted that at least 30 participants are required for a pilot study [33]. We selected the maximum of 30 participants, and the sample size of 60 participants was determined. The results of this study will facilitate the calculation of an appropriate sample size for further randomized clinical trials.

#### Statistical analysis

Analysis will be carried out on an intention-to-treat (ITT) basis and will be performed using SPSS 23.0 statistical software (IBM SPSS Statistics, New York, USA) with a 2-sided *P* value of less than 0.05 considered significant. The measurement of data that conforms to the normal distribution will be expressed as mean ± SD, the measurement data that does not conform to a normal distribution will be expressed by the median (interquartile range), and counting data will be represented by cases (percentages). The continuous variables will be evaluated by using a *t* test or the Mann-Whitney *U* test for comparison. The chi-square test or Fisher’s exact test will be employed to compare binary variables. Missing data will be imputed using the last observation carried forward.

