Acupuncture as a non-pharmaceutical therapy is widely used in the treatment of hypertension [16], and some evidence suggests potential effectiveness [17]. Transcutaneous electric acupoint stimulation (TEAS), a noninvasiveness therapy similar to acupuncture, is used as a clinical alternative to electrical acupuncture and manual acupuncture [18]. It is considered a combination of transcutaneous electrical nerve stimulation and acupuncture. Transcutaneous electrical stimulation therapy has the advantages of being easy to use, which is more “user friendly” requiring minimal training for physicians and patients, and if convenient for clinical application [19]. Two trials have explored the efficacy of simple transcutaneous electrical nerve stimulation based interventions for adults with or without hypertension to reduce blood pressure [20, 21]. And choosing acupoints with antihypertensive effect based on traditional Chinese medicine theory for stimulation may increase the effect of transcutaneous electrical nerve stimulation. Previous studies have shown that TEAS has effects on the nervous system that include regulation autonomic nervous system function and enhancement of the activity of the vagus nerve, thereby potentially affecting BP [22]. This approach was supported by the studies of Jacobsson et al. [23] and Zhang et al. [24] using the Hans electrical stimulator treating acupoints on the forearm showed significant reduction in blood pressure. However, studies of TEAS for high-normal BP are lacking. The main objective of this preliminary trial is to assess the effectiveness and safety of TEAS combined with lifestyle modification in participants with high-normal BP, to calculate the sample size for a future efficacy study.

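### The observed distribution, not the plan, settles how the primary SBP change is summarised and, by implication, tested, so the mean difference and SD that the pilot needs may not be reported

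*Protocol article*

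**What the plan says.** In the protocol article, the Primary outcome section states: "The primary outcome will be the change in mean SBP from baseline to 12 weeks". The same section defines each visit's value: "the final BP will be calculated by removing the initial reading and calculating the mean from the two remaining readings".

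The Statistical analysis section then gives one rule for continuous data of every kind. On one branch, "The measurement of data that conforms to the normal distribution will be expressed as mean ± SD"; on the other, "the measurement data that does not conform to a normal distribution will be expressed by the median (interquartile range"). The test sentence reads: "The continuous variables will be evaluated by using a *t* test or the Mann-Whitney *U* test for comparison". The threshold is a "2-sided *P* value of less than 0.05 considered significant". The section does not set the primary outcome apart from the secondary ones, and it gives no criterion for normality.

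The Background says that one purpose of the trial is "to calculate the sample size for a future efficacy study". The Sample size section repeats that purpose and sets 60 participants, 30 per group.

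**The concern.** Whether 12-week SBP changes look normal can be judged only on the trial's own outcome data. Under the printed rule, the quantity reported for the primary outcome therefore depends on those data. If they are judged non-normal, the reader gets medians, interquartile ranges and a rank-test P value. A rank test does not test a difference in means, and a median with an IQR supplies neither a mean difference nor an SD.

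Two things are at stake. The primary endpoint is worded as a mean, and one branch does not estimate it. The pilot is also meant to inform the size of a later trial, and a calculation for a difference in mean SBP starts from a mean difference and an SD.

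This is not a detail left to an unseen analysis plan. The article prints the rule. A fuller document that followed it would still let the data choose, and one that fixed a mean difference would depart from it.

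**Working it through.** **What the text fixes**

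| Item | Normal branch | Non-normal branch | Stated or implied |
|---|---|---|---|
| Summary | mean and SD | median and IQR | stated |
| Test | t test | Mann-Whitney U | implied by the parallel wording |
| Mean difference available | yes, from the two means | no | follows |
| SD for sizing | yes | no | follows |

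Read literally, the *or* between the two tests has no criterion at all.

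**Inputs from the article:** 30 per group (2 × 30 = 60, which agrees with the stated total); two-sided 0.05. The article gives no effect size, SD or power, so there is no power calculation to reproduce.

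**Assumptions, not in the article:** Shapiro-Wilk at 5% in each arm as the check, with Mann-Whitney used if either arm fails; SD of change 10 mmHg; true difference 0 or 5 mmHg (0.5 SD); the distribution shapes below. There were 10,000 simulated trials per scenario, so the Monte Carlo standard error of a rate near 0.05 is √(0.05 × 0.95 / 10,000) = 0.0022.

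**1. How often the check switches the analysis.** With exactly normal data, P(at least one arm fails) = 1 − (1 − 0.05)² = 1 − 0.9025 = 0.0975. Simulated rates, with no effect and with 5 mmHg:

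| Shape of the change | No effect | 5 mmHg |
|---|---|---|
| Normal | 10.1% | 9.2% |
| Normal, 15% set to zero by carrying baseline forward | 27.0% | 29.0% |
| t, 5 df | 43.8% | 44.6% |
| Skewness 1 | 68.4% | 69.3% |

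The rate depends on the form of the check. One check on pooled residuals, with no effect, gives 5.0% (normal) and 39.6% (t, 5 df).

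**2. How often the switch changes the conclusion.** Two things must happen together: the check fires, and the two tests fall on opposite sides of 0.05. At 0.5 SD, separate simulations put this joint event at 1.1% to 1.2% of trials (normal) and 7.2% to 7.4% (t, 5 df). With no effect it is 0.4% and 1.8%.

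**3. Type I error and power**

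| Shape | Type I: t test alone | Type I: with the check | Power at 5 mmHg: t test alone | Power: with the check |
|---|---|---|---|---|
| Normal | 0.049 | 0.050 | 0.471 | 0.472 |
| t, 5 df | 0.054 | 0.053 | 0.486 | 0.533 |
| Skewness 1 | 0.050 | 0.055 | 0.482 | 0.532 |
| Normal, 15% zeros | 0.049 | 0.050 | 0.418 | 0.410 |

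Type I error stays near 5% either way. A repeat of the t (5 df) scenario gave power of about 0.48 against 0.53.

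**4. Why the SD must be reported.** For a later trial, n per arm = 2(1.960 + 0.842)² × SD² / δ². With δ = 5 mmHg and 80% power (both assumed), an SD of 8, 10 or 12 mmHg gives 41, 63 or 91 per arm. The planned size moves with the square of a quantity that the median branch does not report.

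**The case against.** **The check is partly inferred.** The article ties normality only to how data are expressed. The link to the test, and the idea of a formal preliminary test, are readings of the text. This stands, and the rates above rest on an assumed check. It does not rescue the rule: the choice of summary is stated to depend on the distribution, and without the implied link the choice of test has no criterion.

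**Mean SBP may be the within-visit mean of two readings.** On that reading a rank test of each participant's change would not contradict the endpoint. The reading is possible, though the group-level mean change is the more natural one. Sizing a trial on mean SBP needs a mean difference and an SD under either reading.

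**The article condenses a fuller protocol.** The absence of a named model or interval is therefore not the fault. The fault is the printed rule.

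Three stronger conclusions are tempting and are not supported:

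- *A reader might infer inflated false positives.* The procedure with the check stays near 5%. Only choosing the smaller of the two P values would raise the rate, to 0.058 to 0.067, and nothing in the article says that this is intended. It also states that the trial statisticians are blinded.
- *A reader might infer that the later trial would have to recover an SD from an IQR.* The investigators hold the individual data and can compute the SD directly. The point concerns what the plan commits to report.
- *A reader might infer that switching has no merit.* With t (5 df) tails it has more power than the t test alone.

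**Conclusion.** The point holds in a limited form. As written, the rule lets the observed distribution choose the summary of the primary outcome and, by implication, its test. Followed as printed, it can leave the primary result without a difference in mean change or an SD, although the endpoint is worded as a mean and the trial is meant to size its successor.

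Under the assumed per-arm Shapiro-Wilk check, the effect measure would switch in about 10% (normal) to 44% (t, 5 df) of trials, and in more with marked skewness. The significance call at 0.5 SD would change in about 1% to 7%. The harm is a shifting effect measure and an open choice of primary test, not type I error. In a 60-person pilot with no power claim this does not threaten validity, but it is worth correcting because the correction is nearly free.

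**What to change.** For the primary outcome, and for the other SBP and DBP changes:

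- Name one mean-based analysis in advance.
- Whatever the distribution, report the between-arm mean difference in mmHg with its 95% CI, and the SD in each arm.
- Show the Mann-Whitney result only as a sensitivity analysis, and median (IQR) only as added description.

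This takes one or two sentences in the Statistical analysis section and no new data. The Trial status section says that all 60 participants have been randomised and that follow-up was expected to end in November 2020. The change should therefore be dated and stated to have been made before or after outcomes were compared by arm.

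The statistical cost is some power against a rank test if the changes are heavy-tailed (about 0.48 against 0.53 in the t, 5 df scenario), and essentially none if they are normal.
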